### Sample size estimation

In a 12 month period, 200 people are expected to have a positive FOBt as part of the screening programme and be referred to Wolverhampton Screening Centre.

Our pilot data indicates that elevated MMP9 has a high sensitivity and negative predictive value. The potential of measuring MMP9 in FOBt positive people will be to reduce the number of unnecessary colonoscopies i.e. a high NPV is required. The pilot data indicated that 126 test negative patients are needed to detect a NPV of 95% with 5% precision and 2-sided alpha of 1%. Based on this data, a total of 209 patients are required to enable 91% and of 31% prevalence.

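### The 126 test negatives come from the simple normal formula; at 99% confidence they leave a lower NPV limit about 7 to 8 points below the estimate, not 5

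*Protocol article*

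**What the plan says.** The Sample size estimation section of the protocol article gives the purpose of MMP9 testing in FOBt-positive people as to "reduce the number of unnecessary colonoscopies i.e. a high NPV is required". It then states that "126 test negative patients are needed" for an "NPV of 95% with 5% precision and 2-sided alpha of 1" per cent. A total of 209 patients is built on that figure. The section names neither the formula nor the type of confidence interval, and it states no minimum acceptable NPV.

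**The concern.** An NPV of 95% with a margin of 5 points puts the upper end of a symmetric interval exactly at 100%. The usual normal approximation is poor there, because the sampling distribution of a proportion near 1 is skewed towards lower values. If 126 was obtained that way, the quoted precision is not what 126 patients deliver at 99% confidence.

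The direction matters. When a negative test is meant to spare someone a colonoscopy, the lower NPV limit carries the conclusion. A reader who takes the section at face value would expect a 99% lower limit of about 90%, that is, at most about 10% missed disease among test negatives. A valid interval allows about 12%.

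**Working it through.** **Inputs, all from Sample size estimation.** Anticipated NPV p = 0.95; precision d = 0.05, read as the half-width of the interval; two-sided alpha 0.01, so z = 2.576; test negatives n = 126.

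**1. Reproduce 126.** The normal-approximation formula is n = z²p(1−p)/d². With z² = 6.635 this gives 6.635 × 0.95 × 0.05 / 0.0025 = 126.06. Other choices of alpha and sidedness do not fit: one-sided 1% gives 102.8, two-sided 5% gives 73.0 and one-sided 5% gives 51.4. The formula is inferred from this match, since the article does not name it.

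**2. The interval it implies.** 0.95 ± 2.576 × √(0.95 × 0.05 / 126) = 0.95 ± 0.0500, or 90.0% to 100.0%.

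**3. Its actual coverage.** Summing binomial probabilities over all outcomes at a true NPV of 0.95 with n = 126:

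| Nominal 99% interval | Actual coverage |
|---|---|
| Simple normal | 95.3% |
| Wilson | 98.9% |
| Clopper-Pearson | 99.4% |

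The normal interval misses in about 4.65% of samples. In 4.59 of those percentage points (124 or more of 126 correct) its lower limit lies above the true NPV, against a nominal 0.5% on that side. Nearly all the error therefore overstates how safe a negative test is.

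**4. Valid 99% intervals at n = 126.** An observed NPV of exactly 95% would be 119.7 patients, so the two neighbouring counts are shown. Clopper-Pearson limits are beta quantiles: 0.005 of Beta(x, n−x+1) and 0.995 of Beta(x+1, n−x). Wilson limits are [p̂ + z²/2n ± z√(p̂(1−p̂)/n + z²/4n²)] / (1 + z²/n).

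| Observed | Method | 99% interval | Lower arm (points) | Average half-width (points) |
|---|---|---|---|---|
| 120/126 (95.2%) | Clopper-Pearson | 88.0% to 98.8% | 7.2 | 5.4 |
| 120/126 (95.2%) | Wilson | 87.7% to 98.2% | 7.5 | 5.3 |
| 119/126 (94.4%) | Clopper-Pearson | 86.9% to 98.4% | 7.5 | 5.7 |
| 119/126 (94.4%) | Wilson | 86.6% to 97.8% | 7.8 | 5.6 |

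At a fractional 119.7/126, exactly 95%, the lower limits are 87.7% (Clopper-Pearson) and 87.4% (Wilson), 7.3 and 7.6 points below the estimate.

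**5. Consequence for a 90% lower limit.** If the true NPV is 95%, a sample of 126 gives a 99% lower limit of at least 90% with probability about 24% (Clopper-Pearson) or 12% (Wilson).

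**6. At 95% confidence.** 120/126 gives 89.9% to 98.2% (Clopper-Pearson) or 90.0% to 97.8% (Wilson). At 119/126 the lower limits are 88.9% and 89.0%.

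**The case against.** Several points on the other side are fair.

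- *Nothing is miscalculated.* 126 follows correctly from the stated inputs by a standard planning formula. That stands: the fault lies in the approximation and in the property then claimed for the design, not in the division.
- *The article sets no 90% floor.* This also stands. A reader might infer that the plan undertakes to exclude an NPV below 90% at 99% confidence, and so that the study is too small. The text does not support that: it gives a target and a precision, with no threshold or decision rule. The 90% figure arises only from the plus-or-minus-5 reading, though that is the reading that yields 126. A 99% lower limit of 90% at an observed 95% would take about 226 (Clopper-Pearson, unrounded count) to 239 (Wilson) test negatives, but the article does not commit itself to that aim.
- *Average half-width is close to target.* At 5.3 to 5.7 points it misses 5 only slightly; about 144 to 149 test negatives would bring it to 5. This is true, but a rule-out claim rests on the lower arm, not on the average of the two arms.
- *The shortfall depends on the 1% alpha.* At 95% confidence, 120/126 does reach about 90%. But 1% is the level the article chose.
- *The reported analysis may use a sound interval.* A reader might infer that the results will carry intervals with 95.3% coverage. The Analyses section prescribes no interval method, so this does not follow, and not naming one in an article is no fault. The coverage figure bears on the planning claim only.

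**Conclusion.** The concern holds in limited form. At the 1% alpha stated, 126 test negatives do not give 5-point precision on the lower side. With about 95% observed, the lower limit is about 87% to 88%, an arm of about 7 to 8 points, and the formula behind 126 has about 95.3% rather than 99% coverage at that NPV.

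This rests on two assumptions: that precision means plus or minus 5 percentage points, and that the simple normal formula was used. Both are inferred from the match to 126.06. The finding does not show that the study is too small for an aim it states, nor that its final intervals will be wrong. It shows that one stated property of the design is better than the design can deliver.

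**What to change.** Restate the expected precision in Sample size estimation from an exact or score interval, for example: *126 test negatives with an observed NPV of about 95% (120/126) give an exact 99% confidence interval of about 88% to 99% (95% interval about 90% to 98%).* Giving the count makes clear that the limits belong to 95.2%; one more false negative (119/126) moves the exact 99% interval to about 87% to 98%.

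The cost is one sentence. The change needs no extra patients and does not alter the design or analysis. The stated lower limit becomes about 2 points less favourable than the 90% now implied.

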### Analyses

Patients will be classified into high risk (invasive adenocarcinoma or high risk polyps) and lower risk diagnostic groups. The association between possible risk factors and diagnosis will be determined based on odds ratios (OR). Multivariate logistic regression analyses will determine the independent factors for prediction of high risk disease excluding MMP9 and provide adjusted OR accordingly. The influence of MMP9 will then be assessed by the addition of MMP9 to the derived logistic regression model.

Accuracy and comparison of the predictive models, including and excluding MMP9, will be assessed by the estimates of sensitivity, specificity, proportion of false positives and negatives and overall percentage of correct predictions. Receiver operating curves (ROC) and area under the curve (AUC) of the ROC will be presented for each of the models, including and excluding MMP9, as an indication and comparison of diagnostic ability.

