**Methods and design:**

FOBt positive people aged 60–69 years attending the Wolverhampton NHS Bowel Cancer Screening Unit and providing consent for colonoscopy will be recruited. Participants will provide a blood sample prior to colonoscopy and permission for collection of the clinical outcome from screening unit records. Multivariate logistic regression analyses will determine the independent factors (patient and disease related, MMP9) associated with the prediction of neoplasia.

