## Background

About one in 20 people in the UK will develop colorectal cancer during their lifetime [1]. It is the third most common cancer in the UK, and the second leading cause of cancer death, with over 15,000 people dying from colorectal cancer each year [2]. Colorectal cancer incurs an annual expenditure of more than £300 million in surgical, adjuvant, and palliative treatment [3]. As the population ages these costs are set to increase. Reduced costs of treatment could be achieved by earlier diagnosis. However, most cases are diagnosed at a late stage which is strongly associated with poorer survival; the five year overall survival rate of colorectal cancer is only 48% [4]. Benefits, in terms of improved survival, improved quality of life and reduced treatment costs, could be accrued by earlier diagnosis.

FOBt screening can detect colorectal cancer at an early stage when treatment is more likely to be effective. It also provides an opportunity to identify precursors to invasive disease, polyps, which can be removed during colonoscopy and reduce the risk of colorectal cancer developing. Randomised controlled trials suggest that colorectal screening has the potential to reduce colorectal cancer mortality by 16% [5]. In the light of the evidence from these trials the NHS has introduced a national bowel cancer screening programme [6]. The first UK bowel cancer screening site started screening men and women aged 60–69 years in July 2006 and national coverage is expected to be achieved by 2010. The programme uses the Faecal Occult Blood test (FOBt). Participants in screening, who have a positive FOBt, are then invited for colonoscopy. Pilot evaluations, in Scotland and Rugby, confirmed the feasibility of the national screening programme; however, they also demonstrated relatively low acceptability of FOBt with uptake rates of only 58.5%[7] and 52% [8] in the first and second rounds of screening respectively.

Recent results from the NHS Bowel Cancer screening pilot studies demonstrate that, FOBt testing has a sensitivity of 57.7%, with a positive predictive value of 5.3% for cancer and 38.8% for neoplasia [8]. The low positive predictive value means that although all FOBt positive results require investigation via colonoscopy, many of these are false positive results with the associated cost, risk and anxiety. Colonoscopy carries a risk of bowel perforation of 1 in 1,500 [9].

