### Pilot work

A pilot study of 300 patients attending the Queen Elizabeth Hospital colorectal clinic was performed. Twenty seven significant adenomas and 63 malignancies were identified in the study population. Patients had a standard assessment, by proforma-led history and examination, with rigid sigmoidoscopy to the recto-sigmoid junction. The patients gave serum samples for analysis, and referral for specialist investigations occurred as per the clinic-protocol. Forty-six "normal" volunteers also donated serum. ELISAs were done on each serum sample, and the results were compared with the clinical diagnosis. The median sMMP9 concentration was 443 ngml^-1^. The model accurately predicted neoplasia in 77.3% of cases (sensitivity 77.9%, specificity 77.1%, positive predictive value (PPV) 44.6%, and negative predictive value (NPV) 95.8%) in a population with 30% prevalence of disease [11].

The results of this pilot suggest that MMP9 may be an effective secondary screening test, but this study was completed in a selected population. The performance of a diagnostic test can vary in populations with different severity and prevalence of disease and, therefore, the acceptability and accuracy of MMP9 needs to be established in the target population [14].

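### The regression predicts neoplasia in the abstract but high risk disease in the Analyses section, and the 31% planning prevalence is tied to neither, so the stated NPV precision is unverified for the analysed outcome

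*Protocol article*

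**What the plan says.** The protocol article states the outcome of its regression twice.

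- Abstract, Methods and design: "Multivariate logistic regression analyses will determine the independent factors (patient and disease related, MMP9) associated with the prediction of neoplasia".
- Analyses: "Patients will be classified into high risk (invasive adenocarcinoma or high risk polyps) and lower risk diagnostic groups", and then "Multivariate logistic regression analyses will determine the independent factors for prediction of high risk disease excluding MMP9". MMP9 is added to that model afterwards.

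Three other places bear on prevalence.

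- Background, on FOBt in the NHS pilot studies: "positive predictive value of 5.3% for cancer and 38.8% for neoplasia".
- Pilot work: "Twenty seven significant adenomas and 63 malignancies were identified in the study population", among 300 patients at a hospital colorectal clinic. The text calls the predicted outcome neoplasia and gives a prevalence of 30%, sensitivity 77.9% and specificity 77.1%.
- Sample size estimation: 126 test-negative patients for an NPV of 95% with 5% precision and 2-sided alpha of 1%, and then "209 patients are required to enable 91% and of 31% prevalence". The 31% has neither a named condition nor a source.

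**The concern.** The study is sized on NPV, because its purpose is to spare FOBt-positive people unnecessary colonoscopies. NPV depends directly on who counts as diseased. An MMP9-negative person with a low-risk adenoma is a missed case if the target is any neoplasia, and a correct negative if the target is cancer or high risk polyps.

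The article does not say whether neoplasia in the abstract is meant broadly or in the pilot's narrower sense. Nor does it say which condition the 31% describes. A reader therefore cannot tell what NPV, with what precision, 209 patients are expected to give for the outcome that will be analysed.

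**Working it through.** **1. The stated size.** For a single proportion, n = z² × NPV × (1 − NPV) / d². With z = 2.5758 (2-sided 1%), NPV = 0.95 and d = 0.05:

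n = 6.635 × 0.95 × 0.05 / 0.0025 = 126.06. This agrees with the stated 126.

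The article does not show how it reaches 209. A route that fits divides 126 by the expected share of test negatives, p(1 − Se) + (1 − p)Sp, using the pilot Se = 0.779 and Sp = 0.771 and p = 0.31:

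0.31 × 0.221 + 0.69 × 0.771 = 0.0685 + 0.5320 = 0.6005, and 126 / 0.6005 = 209.8.

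This route is inferred. The 91% in the same sentence has no label and is not used here.

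**2. What the pilot's neoplasia covers.** (27 + 63) / 300 = 90 / 300 = 30%, the stated pilot prevalence. The pilot's cases are therefore malignancies plus significant adenomas, which is close to the high risk class in Analyses, although the article does not equate the two.

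**3. What is known for FOBt-positive people.** The documents give 38.8% for neoplasia and 5.3% for cancer. If high risk polyps are a subset of neoplasia, the prevalence of high risk disease lies between these figures. The value 31% is inside that range, but nothing in the article places it there for this population.

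**4. Implied NPV and its precision with 209 patients.** Pilot sensitivity and specificity are held fixed.

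- NPV = (1 − p)Sp / [p(1 − Se) + (1 − p)Sp]
- Half-width (99%) = 2.5758 × √[NPV(1 − NPV) / m], where m = 209 × share of test negatives

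| Prevalence p | Diseased, 209 × p | Share negative | m | NPV | 99% half-width |
|---|---|---|---|---|---|
| 5.3% (cancer only) | 11 | 0.7419 | 155 | 98.4% | 2.6 points |
| 31% (planning figure) | 65 | 0.6005 | 126 | 88.6% | 7.3 points |
| 38.8% (neoplasia) | 81 | 0.5576 | 117 | 84.6% | 8.6 points |

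At 31%, for example: NPV = 0.5320 / 0.6005 = 0.886, and the half-width is 2.5758 × √(0.886 × 0.114 / 125.5) = 0.073.

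The first row is only a rough guide. It expects about 209 × 0.053 × 0.221 = 2.4 false negatives, and the symmetric interval runs past 100%.

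**5. Two sources of the gap.** The step from 5 to 7.3 points arises because an NPV of 95% does not follow from the pilot accuracy at 31% prevalence. On that accuracy it needs a prevalence of about 15.5%: odds = (0.05 / 0.95) × 0.771 / 0.221 = 0.184, and 0.184 / 1.184 = 0.155. The further step from 7.3 to 8.6 points is the effect of using the neoplasia figure in place of 31%.

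**The case against.** The Methods fix the outcome before any data are seen and state it in two sentences, while the conflict comes from one word in an abstract. In the pilot section that word covers only cancer plus significant adenomas, so the authors may mean the same thing throughout. Between 31% and 38.8% the NPV moves by 4.0 points (88.6 − 84.6), which is less than the 5-point precision. Definitions of lesion classes commonly sit in the full protocol.

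Much of this stands, and it rules out several stronger readings that a reader might infer.

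- *That planning rests on a broader outcome than the one analysed.* The pilot's 30% already counts only significant adenomas and malignancies. The match is unverified, but it is not shown to fail.
- *That 31% fits neither definition in the target population.* The prevalence of high risk disease in FOBt-positive people is not given, so this cannot be shown.
- *That the choice of outcome stays open until the data are seen.* The Analyses section settles it.
- *That 209 yields too few test negatives.* At any prevalence of 31% or below it gives about 126 or more. At 38.8% it gives about 117, and at an NPV of 95% the half-width would be 2.5758 × √(0.0475 / 116.5) = 5.2 points.
- *That the few cancers expected make the study underpowered.* About 11 are expected (209 × 0.053), but no cancer-only analysis is promised.

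The missing definition of high risk polyps in a condensed article is also no fault. What the objection does not remove is that the article names the outcome of one model in two ways, and that the prevalence behind its sample size belongs to no stated condition.

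**Conclusion.** The point holds at moderate severity. The abstract and the Analyses section name different target conditions, and a low-risk adenoma may change sides between them. The planning prevalence of 31% lies next to the clinic pilot's 30%, and the article does not link it to high risk disease in FOBt-positive people. On the pilot accuracy, 209 patients would give an NPV of about 88.6% ± 7.3 points at 31%, or 84.6% ± 8.6 points at 38.8%. The plan states 95% ± 5.

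These figures rest on a normal approximation at 99% confidence and on the pilot sensitivity and specificity carrying over unchanged. The second assumption is weak. Cancers were 63/90 = 70% of pilot cases but 5.3/38.8 = 14% of neoplasia among FOBt positives, and the article itself warns that performance varies with severity and prevalence. The calculation varies prevalence only. It does not measure how sensitivity and specificity would change if low-risk adenomas moved from one group to the other.

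**What to change.** 1. Name high risk disease, as in Analyses, as the single primary target condition in the abstract, the sample size section and the Analyses section. Make any neoplasia a named secondary analysis.
2. State which condition the planning prevalence refers to. Replace the single 31% with the expected NPV and its precision for 209 patients over the document's own range of 5.3% to 38.8%.
3. Tabulate the MMP9 result by cancer, high-risk polyp, low-risk adenoma and none, with exact confidence intervals, so that NPV can be read under either definition.

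The cost is some rewording and one more table, drawn from diagnoses that the study already collects. No extra patients or data are needed. The downside is that the stated precision becomes less favourable over the upper part of the prevalence range.

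### The models with and without MMP9 are judged in the same patients used to derive them, so AUC and accuracy are overstated and a small AUC rise is not evidence of added value

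*Protocol article*

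**What the plan says.** The outcome is binary: "Patients will be classified into high risk (invasive adenocarcinoma or high risk polyps) and lower risk diagnostic groups" (Analyses). The clinical model comes first: "Multivariate logistic regression analyses will determine the independent factors for prediction of high risk disease excluding MMP9". MMP9 then enters as one extra term: "The influence of MMP9 will then be assessed by the addition of MMP9 to the derived logistic regression model". The models are compared on sensitivity, specificity, false-positive and false-negative proportions and percent correct, and the "area under the curve (AUC) of the ROC will be presented for each of the models, including and excluding MMP9".

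There is one cohort from one screening unit. Under Sample size estimation, "In a 12 month period, 200 people are expected to have a positive FOBt", and the requirement is given in a garbled sentence: "a total of 209 patients are required to enable 91% and of 31% prevalence". The size is justified only by the precision of a negative predictive value, not by the needs of model building. The article mentions no second sample, cross-validation, bootstrap or shrinkage, and it lists neither the candidate factors nor the probability cut-off at which sensitivity and specificity will be read.

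**The concern.** A model whose terms are picked and whose coefficients are estimated in a set of patients fits the chance features of those patients. Its AUC, sensitivity, specificity and percent correct in the same patients therefore exceed what it would achieve in the next screening round. The excess grows as the number of cases per candidate factor falls.

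Two things are at stake. The first is the absolute performance that readers would carry over to the screening programme. The second is the contrast between the two models, which bears directly on the study aim. That contrast is taken between two apparent values that need not be optimistic by the same amount.

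**Working it through.** **1. The plan's own figures.** Inputs from Sample size estimation: NPV 95%, half-width 5%, two-sided alpha 1%, prevalence 31%. From Pilot work: sensitivity 77.9%, specificity 77.1%.

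- Test negatives: n = z² p(1−p)/d² = 2.5758² × 0.95 × 0.05 / 0.05² = 126.06. The stated 126 is reproduced.
- Share testing negative: 0.31 × (1 − 0.779) + 0.69 × 0.771 = 0.0685 + 0.5320 = 0.6005.
- Total: 126 / 0.6005 = 209.8. The stated 209 is reproduced to within rounding.

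**2. Cases available for modelling.** 0.31 × 209 = 64.8, or 0.31 × 200 = 62 at the expected yearly intake. This takes 31% as the prevalence of the modelled high-risk outcome, which the garbled sentence does not settle. The Background gives screening-pilot predictive values of 5.3% for cancer and 38.8% for neoplasia. These would give 0.053 × 209 = 11 and 0.388 × 209 = 81 cases as outer limits. At 65 cases, an assumed 5, 10 or 15 candidates leaves 13, 6.5 or 4.3 cases per candidate.

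**3. Simulation of the stated procedure.** Assumptions not in the article: independent, normally distributed candidates; backward elimination at p < 0.05; real effects of log odds ratio 0.5, 0.4, 0.3 per SD (set A) or 0.3, 0.2 (set B), with the other candidates null. N = 209, about 31% prevalence, 1000 replicates per setting. MMP9 is then added as pure noise, and each fitted model is also evaluated in 15,000 new subjects.

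| Candidates, effects | Clinical model: apparent / new | Excess | With MMP9: apparent / new | Excess |
|---|---|---|---|---|
| 5, A | 0.684 / 0.643 | 0.041 | 0.690 / 0.640 | 0.050 |
| 5, B | 0.588 / 0.545 | 0.044 | 0.604 / 0.542 | 0.062 |
| 10, A | 0.692 / 0.644 | 0.047 | 0.697 / 0.641 | 0.056 |
| 10, B | 0.602 / 0.547 | 0.055 | 0.615 / 0.545 | 0.070 |
| 15, A | 0.700 / 0.644 | 0.056 | 0.704 / 0.641 | 0.063 |
| 15, B | 0.614 / 0.541 | 0.072 | 0.625 / 0.540 | 0.085 |

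(Excesses were computed before rounding.) A further simulation under similar assumptions gave an excess of 0.03 to 0.08. The working range is therefore 0.03 to 0.085.

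**4. Accuracy at a cut-off.** If the cut-off is chosen in the same data to maximise sensitivity + specificity − 1 (an assumption; no rule is stated), that index is 0.25 to 0.35 apparent against 0.07 to 0.20 in new subjects. Percent correct at a probability of 0.5 is overstated by about 1.5 to 3 points.

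**5. The AUC difference** (with minus without MMP9, where at least one clinical factor was selected).

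| True MMP9 effect (log OR per SD) | Apparent change | Change in new data | Bias |
|---|---|---|---|
| 0 (six settings above) | +0.004 to +0.008 | −0.004 to −0.002 | +0.007 to +0.011 |
| 0.4 (10 candidates, A) | +0.0285 | +0.0263 | +0.002 |
| 0.8 (10 candidates, A) | +0.0828 | +0.0966 | −0.014 |

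For a strong marker, the further simulation gave an apparent gain of 0.088 to 0.097 against a true 0.111, a shortfall of 0.014 to 0.023. The sign reverses because the clinical model carries its own selection optimism. With the 0.8 effect its excess was 0.054, against 0.041 for the model with MMP9.

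For a useless MMP9, the 95th percentile of the apparent gain was 0.016 to 0.032, so gains of that order can arise by chance.

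**6. The test of the added term.** A Wald test of a useless MMP9 at the 5% level rejected in 3.6% to 5.4% of replicates. The Monte Carlo standard error is √(0.05 × 0.95 / 1000) = 0.7 points.

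**The case against.** The strongest reply is that this is silence, not error. The article lists the measures to be presented and does not say they will be left uncorrected. An unseen analysis plan may supply the candidate list, the selection rule, the cut-off and a bootstrap. It is fair not to fault those details for being absent. What remains is that the Analyses section does state a procedure (derive, add, compare in one cohort) which, followed as written, yields inflated figures.

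A second reply is that the step adding MMP9 is sound. This stands. MMP9 is a single pre-named term that is not itself selected, and the test of it held its level.

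A reader might infer that the comparison is stacked in favour of MMP9, particularly because a useless marker raised the apparent AUC in 75% to 77% of simulated studies. That count includes trivially small rises. The mean gain is under 0.01, the article has no rule that any rise counts as success, and a strong marker is understated. A general tilt towards MMP9 is not supported.

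A reader might also extend the point to a cut-off tuned to reach an NPV of 95%. The article states no such rule: 95% appears only as the planning value for precision, and NPV is not among the measures named in the Analyses section.

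**Conclusion.** The point holds in limited form. As written, the performance figures for both models are apparent values, and each AUC is overstated by roughly 0.03 to 0.085. The bias in the AUC difference is secondary and can go either way: about +0.01 for a useless MMP9, about 0.01 to 0.025 too small for a strong one, and close to nil in between. A small AUC rise alone should therefore not be taken as added value, nor does the design make a false claim for MMP9 likely if the term itself is tested.

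The direction of the absolute inflation is secure; its size rests on assumptions. The number, strength and independence of the candidates and the selection rule are not in the article. The 31% may not be the prevalence of the modelled outcome. Fewer cases would make the optimism larger, more cases smaller. If the full analysis plan already provides internal validation, only the wording of the Analyses section needs aligning with it.

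**What to change.** Amend the Analyses section, before outcome data are examined, along these lines:

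- The conclusion on added value rests on the likelihood-ratio test comparing the clinical model with the same model plus MMP9. Preferably the clinical factors are a list stated in advance. If they are selected from the data, state the selection rule.
- AUC, change in AUC, sensitivity, specificity and percent correct are reported with bootstrap optimism correction. Each resample repeats the factor selection, the addition of MMP9 and any choice of cut-off. The mean difference between performance in the resample and in the original data is subtracted from the apparent value.
- Confidence intervals accompany these estimates, including the change in AUC. Uncorrected values may be shown but are labelled apparent.

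The test shows whether MMP9 carries information beyond the clinical factors; the corrected measures show how much, so both are needed. No extra patients, samples or visits are required. The cost is a little more analysis code, lower reported accuracy and, with a pre-stated list, giving up the data-driven search for clinical factors in the primary comparison.
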